### Randomization and blinding

2.5

All eligible participants who provide informed consent are randomized in a 1:1 ratio to either the FSN group (*n* = 22) or the drug group (*n* = 22). Randomization is performed using a random number table with allocation concealment. The randomization sequence (seed 12345) is generated by methodology personnel not involved in treatment or evaluation using SAS 9.4 software, with a total of 44 random numbers selected. Forty-four allocation cards are prepared, each labeled with a sequential number and a corresponding random number. The cards are sealed in opaque envelopes marked with matching sequential numbers. The envelopes are kept by the statistician. Upon enrollment, the methodologist open the envelope corresponding to the participant’s sequential number and assign the participant to a group based on the random number.

Participant recruitment, intervention administration, outcome assessment, and statistical analysis are conducted independently by different researchers. Due to the nature of acupuncture, neither participants nor practitioners are blinded, but they are instructed not to disclose group allocation during follow-up assessments. To minimize measurement and subjective biases, a unified operational manual is developed to standardize all outcome assessment procedures. Outcome assessors and data collectors are blinded to group allocation and underwent a two-day training program, during which they are instructed not to communicate with participants regarding the intervention. Participants are also directed not to disclose their treatment assignments to the assessors and instructed to record symptoms based on actual experiences, avoiding the influence of treatment expectations. Data analysis is performed by blinded statisticians.

## Intervention

3

Before formal intervention, researchers record participants’ demographic and clinical characteristics, including gender, age, allergy history, marital and reproductive history, family history, smoking and alcohol consumption history, past medical history, medication history, and other relevant clinical data. Participants are educated on adherence to scheduled FSN sessions or flunarizine hydrochloride administration and instructed to avoid other migraine treatments that might interfere with efficacy assessment, such as oral analgesics, acupuncture, massage and so on. On study days, participants are advised to abstain from caffeine and alcohol and ensure adequate rest the night before.

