#### Exclusion criteria

2.3.2

Diagnosed with other primary headaches such as neuropathic headache, cluster headache, or tension-type headache;Comorbid secondary headaches or other neurological disorders (e.g., headache due to anxiety, depression, Parkinson’s disease, or intracranial lesions);Uncontrolled or undiagnosed systemic diseases that may interfere with the study, including severe hepatic, renal, cardiovascular, or cerebrovascular diseases; poorly controlled or untreated hypertension (systolic blood pressure exceeding 160 mmHg and/or diastolic blood pressure above 100 mmHg); poorly controlled or untreated diabetes mellitus; malnutrition; hyperthyroidism; or hepatic insufficiency;Comorbid uncontrolled psychiatric disorders;Presence of cervical spine disorders that may affect the assessment of neck and shoulder muscle function.Pregnancy, lactation, or women in the preparation, menstrual, or menopausal phase;Use of prophylactic medications or other treatments for migraine within the past month;History of allergy to the trial medications or contraindications to flunarizine hydrochloride or ibuprofen;Kin lesions at the FSN operation site;Occupations involving driving, working at heights, or other high-risk activities;Refusal to undergo FSN therapy or oral flunarizine hydrochloride.

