### Oral flunarizine hydrochloride

3.2

Participants in the drug group are administered 5 mg flunarizine hydrochloride capsules nightly before sleep for 4 weeks and complete a medication monitoring form after each dose. After the 28th doses, participants will submit their medication monitoring forms to the investigators for review. Close follow-up will be conducted by the investigators during the medication period, and treatment will be immediately discontinued upon occurrence of any adverse events. If necessary, symptomatic treatment will be administered until the adverse events resolve.

Management of Missed Doses: a missed dose is defined as failure to administer the 5 mg dose within a 24-h period. Subjects are required to record each administration in their medication diary. If a dose is missed, no additional dose is to be taken to compensate; instead, the regular dosing schedule is to be resumed at the next planned administration time. All instances of missed doses are recorded in the diary and considered in the adherence analysis.

Study personnel review the medication diaries at each follow-up visit. Adherence is calculated as the percentage of actual doses taken relative to the total planned number of doses (28 doses). Subjects with an adherence rate below 80%were flagged for handling in the sensitivity analysis.

In cases of severe pain (VAS score >8), participants are permitted to take acute analgesic medication. In accordance with the Chinese Guidelines for Migraine Diagnosis and Treatment (25), ibuprofen sustained-release capsules are recommended for pain relief (one capsule per dose, no more than twice daily). If ibuprofen is ineffective, participants could take previously effective analgesics, with detailed records in headache diaries, including drug name, administration time, dosage, and time to headache relief after medication. Prophylactic migraine medications are prohibited.

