### Secondary outcomes

4.2

Migraine-Specific Quality of Life (MSQOL) scores, including three dimensions: functional limitations (the degree to which migraines limit daily activities), dysfunction (the avoidance of certain activities due to the concern of migraine attacks), and emotional impact (the effect of migraines on mood), assessed via 14 items on a 6-point scale (0–5). Scores are calculated for each dimension.Headache diaries, recording daily migraine episodes, including presence/absence of headache, frequency, average duration, and use of acute analgesics (if taken, drug name, dosage, and frequency were documented). The reduction rate in rescue medication use was extracted as an independent outcome measure, calculated as the percentage decrease in monthly medication frequency and dosage from baseline to the end of treatment and throughout the follow-up period.Migraine Disability Assessment (MIDAS): This score evaluates migraine-related disability through five items (including the number of days that work, household chores, and social/leisure activities are affected by migraine; the score ranges from 0 to 270, with higher scores indicating greater disability).The difference in Visual Analog Scale (VAS) scores from baseline at week 4 of treatment.

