This study has several limitations. This study is a single-center trial with a small sample size (*n* = 60), which may be subject to selection bias, thereby limiting the generalizability of its findings to different populations or settings. Due to the inherent characteristics of acupuncture and pharmacotherapy, blinding both practitioners and participants presents considerable challenges, potentially increasing the risk of bias. To mitigate this risk, the intervention operators, outcome assessors, data collectors, and statisticians are all independent researchers. All personnel, except the operators, remained blind to group allocation. Standardized operating procedures are implemented to ensure adherence to treatment and assessment protocols, thereby minimizing unintended influences on outcome measures. The use of rescue medications may interfere with the evaluation of headache intensity and frequency; therefore, the final analysis will comprehensively document and compare intergroup medication usage (dosage, frequency, time to onset). Subsequent studies should establish unified guidelines. Limited by current equipment, near-infrared spectroscopy monitoring focused solely on hemodynamic changes in the prefrontal cortex and did not assess the effects of FSN on other brain regions. As an exploratory study, this trial aimed to investigate whether FSN may reduce patients’ reliance on flunarizine, decrease drug-related side effects, and provide a safe alternative for patients with contraindications to medication. Future large-scale, multi-center clinical trials are warranted to validate the long-term efficacy of FSN and its potential as an adjuvant or first-line treatment.

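### Section 3 tells all participants to avoid oral analgesics, section 3.2 permits them in severe pain under the flunarizine heading only, and the arms covered by the rescue rule are not stated

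*Protocol article*

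**What the plan says.** The opening of section 3 (Intervention) addresses both arms: "Participants are educated on adherence to scheduled FSN sessions or flunarizine hydrochloride administration". In the same sentence they are "instructed to avoid other migraine treatments that might interfere with efficacy assessment, such as oral analgesics, acupuncture, massage and so on". No exception is given and no rescue rule is referred to.

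Section 3.1 (FSN therapy) describes the needling procedure and its schedule and says nothing about acute medication.

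Section 3.2 (Oral flunarizine hydrochloride) opens with the drug arm: "Participants in the drug group are administered 5 mg flunarizine hydrochloride capsules nightly before sleep for 4 weeks". Its last paragraph then states: "In cases of severe pain (VAS score >8), participants are permitted to take acute analgesic medication". Ibuprofen is named first, then analgesics that worked for the participant before, with each use entered in the headache diary.

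Section 4.2 lists rescue use among the secondary outcomes: "The reduction rate in rescue medication use was extracted as an independent outcome measure". It is a percentage fall from baseline in monthly frequency and dosage. The Discussion (section 7) adds: "The use of rescue medications may interfere with the evaluation of headache intensity and frequency; therefore, the final analysis will comprehensively document and compare intergroup" use of such drugs.

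**The concern.** Two operative instructions on the same drugs conflict. A participant in severe pain who follows the opening of section 3 takes no oral analgesic, while one who follows section 3.2 may take one. Because the permission appears only under the drug-arm heading, someone working from the section for each arm could tell FSN participants to abstain and drug-arm participants that rescue is allowed.

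Two things are at stake. First, the primary outcome is the change in monthly migraine days to Day 28, and VAS is a secondary outcome. Both are self-reported, and section 2.5 states that participants and practitioners are not blinded. If rescue rules were applied differently by arm, part of any between-arm difference could come from rescue and not from FSN or flunarizine. Second, the rescue-use outcome is measured against baseline. If participants are told at enrolment to avoid analgesics, or to hold them for pain above a threshold, use may fall because of that instruction.

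**Working it through.** The article gives no figure for rescue use, so there is no stated number to reproduce. The check sets the passages side by side.

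1. **Is there a contradiction?** Section 3 names oral analgesics as an example of what to avoid, for both arms and without exception. Section 3.2 permits them when VAS exceeds 8. The two can be reconciled only by reading section 3.2 as an unstated exception to section 3, and neither section refers to the other. The text is contradictory as written.

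2. **Which arms does the permission cover?** The wording does not settle it.
   - For the drug arm only: it sits under the flunarizine heading, and section 3.1 has no counterpart. Elsewhere in 3.2 the bare word participants plainly means the drug arm, as where they hand in medication monitoring forms after the 28th dose. In 3.1 the same bare word means the FSN arm.
   - For both arms: the rescue sentence does not name the drug group, although the opening of 3.2 does. The same paragraph ends by prohibiting prophylactic migraine drugs. That cannot be a drug-arm rule as written, because the Introduction classes flunarizine as a preventive drug.

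3. **What does the rest of the article imply?** It points to both arms.
   - Section 2.3.2 excludes, before allocation, anyone with "contraindications to flunarizine hydrochloride or ibuprofen".
   - Section 4.2 defines the rescue-use outcome with no arm limit, and the diary records analgesic name, dosage and frequency for all.
   - Section 4.4 documents acute medication use at recurrence, with ibuprofen as the example and no arm limit.
   - Section 7 plans a between-group comparison of rescue use, which presupposes use in both groups.

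   The intent is therefore fairly clear, but it has to be inferred from eligibility, outcome and discussion text. The instruction that staff and participants would act on does not state it.

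4. **Can an effect on the primary comparison be sized?** That would need the rescue rate in each arm, the level of migraine days and the number of days that rescue removes from the count. The article gives none of these. The direction is open as well: more rescue in the drug arm would flatter the comparator, and more in the FSN arm would flatter FSN.

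5. **What happens to the rescue-use outcome?** If the same rule is applied in both arms, its effect is common to both: it enters each arm's fall from baseline, while the between-arm contrast is less exposed. If different rules are applied, the between-arm contrast carries the difference in rules too.

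**The case against.** The strongest reply is that section 3 gives a general default and section 3.2 a specific exception for severe pain, so only a cross-reference is missing. The ibuprofen exclusion, the rescue-use outcome, the recurrence text and the planned between-group comparison all show that rescue was meant for both arms. The trial runs in one hospital, so different sites cannot read the text differently. The diary records analgesic use in both arms, and the Discussion names rescue as a limitation. The detailed handling of rescue in the analysis may properly sit in a statistical analysis plan that is not shown.

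Most of this stands. A reader might infer that the plan gives rescue to the drug arm only. The documents do not support that: no sentence restricts it, and several passages point the other way. A reader might also infer a bias large enough to matter against the 1-day non-inferiority margin. That is unsupported too, because any such figure would rest wholly on assumed inputs. Rescue is permitted only once pain is already severe, so the headache is already present on that day. Its effect on the count would come mainly through preventing carry-over to later days, on which the article gives no data. The lack of a derivation rule for rescue days is likewise no fault in an article.

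What does not fall away is the conflict between the two instructions. Intent inferred from other sections does not replace an instruction that participants and practitioners can follow. Documenting and comparing use describes an imbalance without removing its effect on migraine days or VAS, and the Discussion leaves unified guidelines to later studies.

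**Conclusion.** The point holds as a contradiction between two participant instructions, aggravated by placing the rescue permission under one arm's heading. Unequal rescue access is a risk that the wording creates, not a rule that the plan sets. Its effect on the migraine-day and VAS comparisons has no derivable size or direction. The conclusion rests on the article's own text: the instruction in section 3 covers both arms, participants are unblinded, the outcomes are self-reported, and the article accepts that rescue can interfere with intensity and frequency. The rescue-use outcome is exposed in addition, because its fall from baseline could partly reflect the instruction given. This is an avoidable weakness of wording that should be corrected. It does not show that the primary comparison is biased.

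**What to change.** Reconcile the analgesic sentence in section 3 with the rescue paragraph in section 3.2 into one instruction. Place it in the common part of section 3, word it identically for both arms, and state that it applies to both. Which clinical rule it contains is for the sponsor to decide. The cost is a wording amendment and the matching change to participant and staff instructions; no new data are needed.

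Optionally, as a supportive analysis, count any diary day with both headache and acute analgesic use as a migraine day in both arms. The diary already records both items. This is not a full correction: it does not recover later headache days that rescue prevented, and it leaves VAS untouched.

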### FSN therapy

3.1

Participants are seated while the practitioner identify affected muscles (sternocleidomastoid, scalene, splenius capitis, and upper trapezius) via sliding palpation. The palpation reveal tissue tension, rigidity, firmness, and a smooth, resilient texture, accompanied by cord-like changes. The affected muscle tissues may exhibit localized soreness and discomfort. After disinfection, a disposable FSN needle (diameter 0.60 mm, length 50 mm; Nanjing Paifu Medical Technology Co., Ltd., Jiangsu, China) is inserted parallelly to the subcutaneous loose connective tissue surrounding the affected muscle. Once fully inserted, the soft tube stand is secured in the slot. The operator then perform alternating sweeping motions using the index and ring fingers with an angle of 60°at a frequency of 100 sweeps per minute. This is accompanied by reperfusion activities—resistance-based contraction and relaxation of the affected muscles, performed collaboratively by the practitioner and participant. After 20 sweeping dispersions, a 10-s reperfusion activity is performed, with this procedure repeated 3 times for each affected muscle. Reperfusion methods for specific muscles are as follows:

Sternocleidomastoid: seated, the participant turn the head toward the unaffected side while the practitioner apply resistance to the affected side, prompting the participant to attempt turning toward the affected side.Scalene: seated, the participant tilted the head slightly toward the affected side while the practitioner resist, prompting the participant to attempt further tilting.Splenius Capitis: seated, the participant extend the head maximally (until the line between the ear apex and earlobe was horizontal) while the practitioner resist at the occiput, prompting the participant to attempt further extension.Upper Trapezius: seated, the participant maximally elevate the affected shoulder while the practitioner resist, prompting the participant to attempt further elevation.

The FSN group receive treatment twice weekly for 4 weeks.

### Oral flunarizine hydrochloride

3.2

Participants in the drug group are administered 5 mg flunarizine hydrochloride capsules nightly before sleep for 4 weeks and complete a medication monitoring form after each dose. After the 28th doses, participants will submit their medication monitoring forms to the investigators for review. Close follow-up will be conducted by the investigators during the medication period, and treatment will be immediately discontinued upon occurrence of any adverse events. If necessary, symptomatic treatment will be administered until the adverse events resolve.

Management of Missed Doses: a missed dose is defined as failure to administer the 5 mg dose within a 24-h period. Subjects are required to record each administration in their medication diary. If a dose is missed, no additional dose is to be taken to compensate; instead, the regular dosing schedule is to be resumed at the next planned administration time. All instances of missed doses are recorded in the diary and considered in the adherence analysis.

Study personnel review the medication diaries at each follow-up visit. Adherence is calculated as the percentage of actual doses taken relative to the total planned number of doses (28 doses). Subjects with an adherence rate below 80%were flagged for handling in the sensitivity analysis.

In cases of severe pain (VAS score >8), participants are permitted to take acute analgesic medication. In accordance with the Chinese Guidelines for Migraine Diagnosis and Treatment (25), ibuprofen sustained-release capsules are recommended for pain relief (one capsule per dose, no more than twice daily). If ibuprofen is ineffective, participants could take previously effective analgesics, with detailed records in headache diaries, including drug name, administration time, dosage, and time to headache relief after medication. Prophylactic migraine medications are prohibited.

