## Safety assessment

5

The primary clinical adverse reactions associated with Fu’s acupuncture needling are subcutaneous hemorrhage and needling syncope. Before the procedure, the operator should avoid needling in areas with dense vascularization. Upon completion of each Fu’s acupuncture session, prolonged pressure should be applied to the needle insertion site and along the needle track to prevent subcutaneous hematoma. Subcutaneous hematomas are graded according to the CTCAE criteria as follows: Grade 1 (Mild): Small hematoma with a diameter <2 cm; managed with local compression or observation. Grade 2 (Moderate): Hematoma measuring 2–5 cm; managed with compression, heat therapy, and temporary discontinuation of treatment if necessary. Grade 3 (Severe): Hematoma >5 cm with persistent bleeding; treatment is discontinued, and the patient is referred for clinical management.

In cases of needling syncope, the needles should be immediately removed. The participant should be placed in a supine position with legs elevated, and vital signs should be monitored. Symptomatic management, such as oxygen administration and hydration, should be provided as needed. Severe cases require prompt medical attention.

Flunarizine’s frequent adverse events are sedation, weight gain and extrapyramidal reactions (31). Body weight is measured every 2 weeks (on days 1, 14, and 28) to quantify weight increase (a change of ≥5% from baseline is considered clinically significant). Extrapyramidal symptoms (EPS), including tremor, akathisia, dystonia, and rigidity, are assessed using the Rating Scale for Extrapyramidal Side Effects (RSESE). Evaluations are conducted at baseline, Week 2, Week 4, and during follow-up by trained neurologists.

Criteria for drug discontinuation included persistent sedation (lasting ≥3 days and interfering with daily activities), moderate to severe EPS (CTCAE grade ≥2), or weight gain of ≥7% accompanied by the patient’s request to withdraw. All events are recorded in patient diaries and reviewed weekly by assessors.

All serious adverse events (SAEs) must be reported to the Ethics Committee within 24 h.

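### Sections 3.2 and 5 give different rules for stopping flunarizine, and nothing says which one applies

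*Protocol article*

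**What the plan says.** Section 3.2 (Oral flunarizine hydrochloride) states that "treatment will be immediately discontinued upon occurrence of any adverse events". It sets no grade, duration or causality threshold. The sentence after it adds symptomatic care where needed until the event resolves.

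Section 5 (Safety assessment) says of the same drug: "Criteria for drug discontinuation included persistent sedation (lasting ≥3 days and interfering with daily activities), moderate to severe EPS". The EPS criterion is CTCAE grade 2 or more. The third criterion is "weight gain of ≥7% accompanied by" the patient's own request to withdraw. On weight, the same section says that "a change of ≥5% from baseline is considered clinically significant", so it recognises a notable change that lies below its stopping threshold. It also states that flunarizine's "frequent adverse events are sedation, weight gain and extrapyramidal reactions".

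For FSN, Section 5 gives graded handling only. A grade 1 event is described as "Small hematoma with a diameter <2 cm; managed with local compression or observation". Grade 2 may lead to a temporary pause, and grade 3 ends treatment. For needling syncope the needles come out and symptoms are managed, with no stated end to the course.

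**The concern.** Site staff have two instructions for the same patient. The events on which they differ are mild forms of those the article itself calls frequent on flunarizine, so the conflict is likely to arise in practice.

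The choice also bears on the main comparison. FSN is tested for non-inferiority to flunarizine with a margin of 1 monthly migraine day (Section 2.4), on the change to Day 28 (Section 4.1), with neither participants nor practitioners blinded (Section 2.5). A rule that withdraws the comparator for minor events, with no counterpart in the FSN arm, could shorten flunarizine exposure inside that 28-day window. It could also cut short the exposure over which weight and EPS are assessed at weeks 2 and 4, and the Discussion announces a comparison of adverse-event profiles.

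**Working it through.** No figure in the article depends on this point, so the check is a comparison of text.

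**Step 1: apply both rules to the same flunarizine patient.**

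| Event | Section 3.2 | Section 5 |
|---|---|---|
| One day of mild sedation | Discontinue | No criterion met |
| Grade 1 EPS | Discontinue | No criterion met |
| Weight gain of at least 5% but below 7% | Discontinue, if recorded as an adverse event | No criterion met |
| Weight gain of at least 7%, no request to withdraw | Discontinue, if recorded as an adverse event | No criterion met |
| Sedation of at least 3 days that interferes with activities | Discontinue | Discontinue |
| EPS of grade 2 or more | Discontinue | Discontinue |

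The rules agree in the last two rows and differ in the first four.

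**Step 2: can both stand?** Every event that meets a Section 5 criterion is also an adverse event. If Section 3.2 is followed literally, the drug has already been stopped before any Section 5 threshold can decide anything. The thresholds then have no function. No sentence ranks the two sections or limits Section 3.2 to a hold.

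**Step 3: compare with FSN.** Section 5 lets FSN continue after a grade 1 haematoma, pauses it if necessary at grade 2 and stops it at grade 3. FSN has no any-event stop. Under the Section 5 criteria both arms have threshold-based stopping, so the asymmetry arises only if Section 3.2 is the rule in force.

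**Step 4: what can be said about size.** Let p be the share of the flunarizine arm stopped early and f the fraction of the drug effect that they lose. With participants analysed as randomised, the comparator mean falls by p × f × 1.9 days, where 1.9 is the flunarizine reduction assumed in Section 2.4. The article gives neither p nor f. Setting f = 1 (total loss of effect) gives only a ceiling for each assumed p:

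- p = 10%: 0.10 × 1.9 = 0.19 days
- p = 20%: 0.20 × 1.9 = 0.38 days
- p = 30%: 0.30 × 1.9 = 0.57 days
- p = 40%: 0.40 × 1.9 = 0.76 days

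These p values are assumptions with no source in the article, and f = 1 is a worst case. The lines show direction and dependence; they are not estimates.

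**Step 5: a consequence for adherence.** Section 3.2 flags drug-arm participants below 80% of 28 doses for a sensitivity analysis. Since 22/28 = 78.6% and 23/28 = 82.1%, anyone stopped for good after 22 or fewer doses is flagged. Which stopping rule is used therefore also affects who is flagged.

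**The case against.** The best defence is that the sections can be read together. Section 3.2 does not say that the stop is permanent and goes on to describe care until the event resolves. Section 5 itself uses the idea of a temporary discontinuation for a grade 2 haematoma. Its drug criteria are introduced by a word that may signal an open list. On that reading, Section 3.2 is an immediate hold and Section 5 governs permanent withdrawal. This is possible, but the article does not say it. An open list would not help either, because adding further criteria does not explain why duration and grade thresholds are needed if any event already suffices.

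It is also fair to say that some difference in handling is to be expected between a local needle-site bruise and systemic effects of a nightly drug. That stands: the difference between arms is a possible consequence of the Section 3.2 wording, not a separate defect.

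The point concerns two printed rules that disagree. The fact that an article condenses a fuller protocol does not answer it.

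**Conclusion.** The contradiction is real and should be resolved: for mild sedation and grade 1 EPS the two sections give opposite instructions, with no order of precedence. This rests on the wording alone.

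The effect on the trial result is conditional and qualitative. A shift towards FSN requires that Section 3.2 is the rule applied, that the stop is lasting, that stopped participants are analysed as randomised, and that they lose material benefit by Day 28. The article settles none of these.

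Two stronger readings are tempting and unsupported. A reader might infer that the comparison is already biased towards FSN; without an event rate or a stated duration of the stop, that cannot be shown. A reader might also set the number of likely stops against the 25% dropout allowance in Section 2.4 (22 × 0.25 = 5.5 per arm). Stopping the capsules is not loss to follow-up, and nothing in the article says that such a participant lacks a Day 28 outcome, so the two should not be compared.

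**What to change.** The clinical lead should reconcile Sections 3.2 and 5 into one unambiguous rule for flunarizine. It should state whether a stop is temporary or permanent and, if it can be temporary, how it relates to the Section 5 criteria. The result should then be checked against the handling of adverse events in the FSN arm, so that any remaining difference between arms is deliberate. This review does not say which rule is right.

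As a secondary addition, state that participants who stop treatment continue the headache diaries and the visits already scheduled in Sections 2.2 and 4.4. This keeps their Day 28 outcome available; it does not undo any loss of comparator exposure.

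The cost is a protocol clarification and a notice to site staff. No new visits or measurements are needed.
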